# Effect of remimazolam versus propofol anesthesia on postoperative delirium in neurovascular surgery: study protocol for a randomized controlled, non-inferiority trial

**DOI:** 10.1186/s13741-024-00415-6

**Published:** 2024-06-14

**Keywords:** Neurosurgery, Neurovascular surgery, Postoperative cognitive dysfunction, Postoperative delirium, Propofol, Remimazolam

## Abstract

**Background:**

Remimazolam is a short-acting benzodiazepine newly approved for the induction and maintenance of general anesthesia. Remimazolam emerges as an ideal drug for the neurosurgical population due to its rapid emergence, enabling early neurological assessment, and its ability to maintain perfusion pressure, which is crucial for preventing cerebral ischemia. However, the use of benzodiazepine has been associated with an increased risk of postoperative delirium (POD). There is currently limited evidence about the relationship between remimazolam-based total intravenous anesthesia (TIVA) and POD.

**Methods:**

In this double-blind, randomized, non-inferiority trial, we plan to include 696 adult patients with American Society of Anesthesiologists physical status class I to III, undergoing elective neurovascular surgery under general anesthesia. After informed consent, the patients will be randomized to receive either remimazolam or propofol-based TIVA with a 1:1 ratio. The primary outcome is the incidence of POD within 5 days after surgery. Secondary outcomes include subtypes, number of positive assessments and severity of POD, emergence agitation, intraoperative awareness and undesirable patient movement, intraoperative hypotension, and postoperative cognitive function. The data will be analyzed in modified intention to treat.

**Discussion:**

This trial will evaluate the effect of remimazolam on the development of POD compared to propofol anesthesia. The results of this trial will provide evidence regarding the choice of optimal anesthetics to minimize the risk of POD in neurosurgical patients.

**Trial registration:**

The study protocol was prospectively registered at the Clinical trials (https://clinicaltrials.gov, NCT06115031, principal investigator: [name]; date of first registration: November 2, 2023, before the recruitment of the first participant.

## Background

Neurovascular surgery needs neuronal evoked potential monitoring to provide real-time feedback for possible nerve damage. Waveforms acquired during evoke potential monitoring, especially motor and sensory evoked potential monitoring, can be adversely affected by inhalational anesthetics (Schindler et al. 1998). Therefore, total intravenous anesthesia (TIVA) using propofol was identified as the preferred method of maintenance during neurosurgery which needs neuromonitoring (Walker et al. 2020).

Remimazolam, a new short-acting benzodiazepine, has recently gained approval as an intravenous anesthetic for the induction and maintenance of general anesthesia. It has high water solubility and is hydrolyzed by tissue esterase into an inactive metabolite, which allows a rapid onset of sedation/anesthesia and prompts arousal despite prolonged use. In addition, it could be rapidly reversible by an antidote of benzodiazepine, flumazenil (Kim 2022). In the American Society of Anesthesiologists (ASA) physical status class I and II patients undergoing general anesthesia, the remimazolam-based TIVA has shown comparable efficacy as a general anesthetic to propofol-based TIVA while demonstrating a superior safety profile (Doi et al. 2020). Remimazolam has exhibited a lower incidence of hypotension, reduced vasopressor requirements, and fewer instances of bradycardia compared to propofol-based TIVA (Doi et al. 2020). Remimazolam would be quite appealing in patients undergoing cerebrovascular surgery because early emergence from anesthesia is critically important for early neurological assessment and maintaining perfusion pressure is essential to prevent cerebral ischemia in this population (Teixeira et al. 2024).

Despite these promising properties of remimazolam as a general anesthetic, however, there is currently limited evidence about the relationship between remimazolam and postoperative delirium (POD). It may mitigate POD risk by averting intraoperative hypotension, yet as a benzodiazepine, it could potentially increase the risk (Inouye et al. 2014; Kappen et al. 2022; Vasilevskis et al. 2012; Wachtendorf et al. 2022).

POD is associated with increased morbidity, mortality, and healthcare costs (Inouye et al. 2014). The 1-year survival probability is reduced by approximately 10% for each additional day of POD (Pisani et al. 2009). Additionally, it is closely related to long-lasting postoperative cognitive dysfunction (Goldberg et al. 2020).

Therefore, the investigators designed this prospective, randomized, double-blinded, active comparator-controlled, non-inferiority trial to investigate the incidence of POD after remimazolam-based TIVA compared with propofol-based TIVA in patients undergoing neurovascular surgery. We hypothesized that the use of remimazolam for general anesthesia would be non-inferior to propofol anesthesia in the incidence of POD. In this report, we outline our approach and study protocol and aim to establish an a priori record of our principal methods and primary endpoints.

## Methods

### Ethics and registration

The ethics committee at Samsung Medical Center approved the study (IRB no. SMC 2023–08-135). The study has been registered on ClinicalTrials.gov on November 2, 2023 (NCT06115031). Written informed consent will be obtained from the patients or legal guardians prior to participation in the study. Trained research assistants will inform the patients of study objectives, benefits, and possible risks and how to react if risks occur. They will discuss the trial with patients and obtain written consent from patients willing to participate in the trial. Consent forms are provided for all patients involved in this trial.

### Study setting

This is a single-center, randomized, parallel-group, non-inferiority trial with the patient- and outcome investigator blinding (Fig. 1). The study will be conducted at Samsung Medical Center, tertiary teaching hospital (Seoul City, Republic of Korea, principal investigator: [name]). The trial will be an investigator-initiated and non-commercial clinical trial. The study design is in accordance with Good Clinical Practice guidelines, the principles of the Declaration of Helsinki, and relevant regulations. The Consolidated Standards of Reporting Trials flow diagram is demonstrated in Fig. 1. The overall schedule is illustrated in Table 1, and the current study protocol is the first version.

**Fig. 1 Fig1:**
[figure not shown]
The Consolidated Standards of Reporting Trials flow diagram

**Table 1 Tab1:** Overall schedule of participants

Timeline	Enrollment	Allocation	Post-allocation							
Timepoint	Within 72 h of admission	Surgery day	*Postoperative day*							
			*0*	*1*	*2*	*3*	*4*	*5*	*7*	*90*
Enrollment:										
Eligibility screen	X									
Informed consent	X									
Allocation		X								
Interventions:										
Propofol group		X								
Remimazolam group		X								
Assessments:										
Baseline variables	X									
Frailty, fall-down, and functionality assessment	X									X
Cognitive assessment (MoCA)	X								X*	X
Intraoperative data		X	X							
Intraoperative adverse events		﻿X	﻿X							
Delirium assessment (CAM-ICU, 3D-CAM)	X		X	X	X	X	X	X		
Quality of recovery				X						
Pain score and opioid requirement			X	X	X	X	X			
Postoperative neurologic and non-neurologic complications			X	X	X	X	X	X	X	X

^*^If the patient is discharged before POD 7, it is performed before discharge

### Patient recruitment

Screening can be performed either in the outpatient unit or in the ward prior to surgery. The lead investigator will be responsible for screening all adult patients who are scheduled for elective neurovascular surgery (aneurysm clipping, microvascular decompression, superficial temporal artery to middle cerebral artery bypass, arteriovenous malformation removal, etc.). A screening log will be compiled to record their eligibility for study participation. Patients who meet the inclusion criteria but do not belong to the exclusion criteria will be contacted by trained research assistants to obtain written informed consent. The study activities were started in November 2023 and are expected to be completed in October 2025.

### Eligibility criteria for participants

Inclusion criteria are (1) patients aged 19 years old or older, (2) ASA physical status classification I to III, (3) elective neurovascular surgery (aneurysm clipping, microvascular decompression, superficial temporal artery to middle cerebral artery bypass, arteriovenous malformation removal, etc.) and receiving general anesthesia.

Exclusion criteria are (1) severe respiratory disease or cardiovascular disease, (2) severe hepatic (Childs-Pugh Score Class C) disease, (3) severe audio-visual impairments that impede communication, (4) hypersensitivity reactions, allergies, or contraindications to the study drugs, (5) evidence of preoperative delirium in Confusion Assessment Method (CAM), and (6) dependency on psychiatric drugs or alcohol.

Dropout criteria are (1) patient withdrawal and (2) surgery cancelation. In participants who withdraw their consent, the reason for their withdrawal will be collected and reported. They will also be asked to specify which aspects of the trial they are withdrawing their consent and participation from. They will be included in the final report of the trial to ensure complete transparency. A participant who withdraws consent for follow-up assessment will be asked about the use of outcome data and only permitted data will be used for the final analysis. All data will be analyzed according to the modified intention to treat (ITT) principle after excluding patients with drop-out criteria.

### Randomization and blinding

Patients will be randomly allocated to either the propofol or remimazolam group in a 1:1 ratio. Block randomization with random permuted block sizes of 4, 6, and 8 was used to ensure a similar number of subjects in each arm over time while minimizing predictability. A randomization code will be generated on the website (sealedenvelope.com) by an independent research assistant who will not be involved in patient care, pack the allocation group in sequentially numbered, opaque envelopes with identical shapes and sizes, and then give the envelope to attending anesthesiologist and nurse. The investigators who will enroll study participants will be blinded to the group allocation.

The group allocation will be blinded to the people as follows: (1) patients: patients are under general anesthesia during the intervention, (2) surgeons: the anesthesia process is initiated prior to the surgeon’s entry into the operating room. This is followed by the placement of opaque drapes that effectively prevent the surgeon from observing any details of the anesthesia technique. The opaque drapes remain in place from the induction of anesthesia throughout the entirety of the surgical procedure, (3) attending anesthesiologists: Anesthesiologists in the operating room cannot be blinded to randomization assignment but are not involved in the study enrollment or assessment of the results, (4) the outcome assessor will be blinded to the group allocation and evaluate the postoperative outcomes. Group allocation is only opened when all the collected data are ready for statistical analysis.

In a medical emergency, such as deterioration of the patient’s condition intraoperatively or adverse events postoperatively, the blindness will be unmasked by the request from the attending anesthesiologist to the principal investigator.

### Preoperative evaluation

Patient’s baseline demographic data will be collected and entered into a predetermined case report form (CRF), which includes the presence of delirium, sensory impairment (Morandi et al. 2021), alcoholism, history of depression, history of falls within 6 months, history of obstructive sleep apnea, level of education, functional status determined by the Barthel Activities of Daily Living index score (Mahoney and Barthel 1965), frailty score (Abellan van Kan et al. 2008), Charlson’s comorbidity index (Quan et al. 2011), type of surgery, neurologic deficit, polypharmacy (Hein et al. 2014), regular use of cholinergic antagonists, dopamine agent, lithium, benzodiazepine drug, floroquinolone, corticosteroid, or opioid analgesics. Preoperative laboratory results, including electrolytes and blood counts, will be recorded.

### Intervention

Patients in the remimazolam group will be administered a loading dose of 0.1 − 0.2 mg/kg intravenously, followed by a continuous infusion of 1 − 2 mg/kg/h until the end of surgery. Flumazenil (100 − 500 mcg) will be administered to wake the patients at the end of surgery until they show eye-opening and simple obeying. Patients in the propofol group will receive general anesthesia using a target-controlled infusion (TCI) of propofol with an effect site concentration of 3 − 5 μg/mL until the end of surgery. In both groups, remifentanil will be co-administered using a TCI mode. Anesthetics in each group will be adjusted by attending anesthesiologists with reference to the bispectral index (BIS), heart rate, and blood pressure.

### Anesthetic care

Patients will not receive any premedication (usually including anticholinergics and sedatives). On arrival at the operating room, the patient will be applied standard monitoring including pulse oximetry, non-invasive arterial blood pressure, and electrocardiography. Anesthesia will be induced and maintained with study drugs with respect to the group allocation, propofol or remimazolam. To facilitate endotracheal intubation, 0.6–1 mg/kg of rocuronium will be administered and mechanical ventilation will be carried out with a tidal volume of 8 mL/kg, inspiratory: expiratory ratio of 1:2, a fraction of inspired oxygen of 0.5 supplemented with air, and positive expiratory pressure of 5 cmH_2_O. The respiratory rate will be modified to maintain normocarbia. The anesthetic depth will be monitored using a BIS monitor (BIS™; Medtronic, Dublin, Ireland) and maintained between 40 and 60. Continuous invasive blood pressure monitoring using an arterial catheter will be performed. Blood pressure and heart rate will be maintained within 20% of baseline during the surgery. Attending anesthesiologists will be discouraged from administering anticholinergics and intravenous hypnotic agents (e.g., midazolam, ketamine, dexmedetomidine, etomidate) except for their study drugs during the maintenance period. In case of bradycardia, glycopyrrolate or atropine will be administered, and their dose will be recorded. At the end of the surgery, 5-hydroxytryptamine 3 receptor antagonists will be administered as prophylaxis for postoperative nausea and vomiting, and 0.01 mg/kg hydromorphone will be administered for pain control. Sugammadex will be administered for the reversal of neuromuscular blockade. After confirming the reversal of neuromuscular blockade and the patient’s obeying, the patients will be extubated and transferred to the ICU. If the patients cannot obey or in case of surgeon’s request, they will be transferred to the ICU with intubated state.

### Postoperative care

Postoperatively, acetaminophen (1 g) or ketorolac (30 mg) will be administered if the patient presents with moderate pain (numeric rating scale, NRS ≥ 4) unless patients have any contraindication for each drug. Additionally, 25 mg of pethidine or 1 mg of hydromorphone will be administered as a rescue opioid. Other perioperative management will be provided according to the institutional protocol.

The researchers will take appropriate measures for injuries deemed to have directly resulted from this clinical trial. In the event of sustained harm, compensation will be offered by utilizing resources in accordance with the participant compensation provisions outlined by the investigator-initiated clinical trial program of Samsung Medical Center. The criteria for compensation disbursement/exclusion will follow the compensation protocol submitted to an institutional review board of Samsung Medical Center.

### Outcomes

#### Primary outcome

The primary outcome is the incidence of POD as defined by any positive assessment between 2 h after surgery and postoperative day 5 or discharge, whichever comes first.

#### Secondary outcomes

Secondary outcomes are (1) severity of delirium, (2) number of positive delirium assessment, (3) emergence agitation which is defined as RASS + 1 or more within 30 min after the endotracheal extubation, (4) delayed extubation (> 1 h after surgery), (5) perioperative adverse events including intraoperative awareness with recall or undesirable patient movement, bradycardia with the use of chronotropic agent, laryngeal spasm, bronchospasm, allergic reaction, arrhythmia, cardiac events (myocardial infarction, vasospasm, or cardiac arrest), or massive bleeding, (6) area under the mean blood pressure threshold (AUT), (7) quality of recovery using Qor-15 questionnaire (Stark et al. 2013), (8) postoperative nausea and vomiting (PONV), (9) incidence and severity of non-delirium complications (non-neurologic or neurologic) within 30 days after surgery, which are graded using Clavien-Dindo classification (Dindo et al. 2004; Landriel Ibañez et al. 2011), (10) length of hospital, defined as the number of days from index neurovascular surgery until initial hospital discharge and ICU stay, defined as the number of hours in the neurosurgical ICU following index neurovascular surgery until the initial ICU discharge, (11) changes in cognition. (12) The occurrence of fall-down and associated injury and functionality at 3 months after surgery.

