#### Adverse events

Perioperative adverse events, which include bradycardia, laryngeal spasm or bronchospasm, allergic reaction, arrhythmia, cardiac events (myocardial infarction, vasospasm, or cardiac arrest), or massive bleeding, will be monitored by the research team and all serious adverse events will be reported to the institutional review board (IRB). The duration and severity of intraoperative hypotension will be assessed using an area under a mean arterial pressure threshold which is defined as the depth below the threshold multiplied by duration, expressed as mmHg * Time (Liem et al. 2020). Awareness with recall will be assessed using the Modified Brice Questionnaire at least 6 h after the end of surgery when the patients are fully alert (Brice et al. 1970). The patient who develops delirium will be assessed following delirium resolution. Undesirable patient movement during surgery will be recorded and graded following criteria. Mild: undesired spontaneous breathing or non-purposeful movement with no impact on the surgery or patient outcome. Moderate: movement that mildly impacted the surgery (e.g., required a pause in the surgery for coughing or straining) and required deepening of anesthesia, deepening of analgesia, or increased muscle relaxant. Severe: movement with a marked negative impact on the surgery (e.g., a patient injury, loss of sterility of the surgical field, purposeful movements suggestive of awareness, or other surgical complication (Wildes et al. 2019).

Postoperative neurologic and non-neurologic complications will be assessed using the example of complication grades proposed to define and grade neurosurgical postoperative complications based on the Clavien-Dindo classification (Landriel Ibañez et al. 2011).

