#### Intraoperative data collection

Intraoperative measures, including operative and anesthesia time, anesthetic concentration, perioperative use and dosage of sedatives and opioids, electroencephalographic (EEG) data, hemodynamic data, use of inotropic or vasopressor agents, use of a chronotropic agent for the treatment of bradycardia, total infused volume of crystalloid, transfusion, estimated blood loss, and urine output, will be obtained from patients’ electronic medical records.

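### Bradycardia counts as a secondary event only if it was treated, and treatment is decided by unblinded anesthesiologists without a stated heart-rate trigger

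*Protocol article*

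**What the plan says.** All references are to the protocol article.

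- **Secondary outcomes.** The bradycardia component of the perioperative adverse events is "bradycardia with the use of chronotropic agent". Delayed extubation is defined as more than 1 h after surgery.
- **Adverse events.** The corresponding list has no drug condition: "Perioperative adverse events, which include bradycardia, laryngeal spasm or bronchospasm, allergic reaction, arrhythmia". A moderate undesirable movement is one that mildly affected the surgery and also "required deepening of anesthesia, deepening of analgesia, or increased muscle relaxant". In the same section, hypotension is measured from recorded pressure, as an area below a mean arterial pressure threshold.
- **Anesthetic care.** "Attending anesthesiologists will be discouraged from administering anticholinergics" during maintenance; then, "In case of bradycardia, glycopyrrolate or atropine will be administered, and their dose will be recorded". No heart rate is given that makes an episode a bradycardia. On extubation: "If the patients cannot obey or in case of surgeon’s request, they will be transferred to the ICU with intubated state".
- **Randomization and blinding.** The attending anesthesiologists "cannot be blinded to randomization assignment but are not involved in the study enrollment or assessment of the results". The surgeon is described as blinded by opaque drapes. The blinded assessor evaluates postoperative outcomes.
- **Data collection.** Perioperative data are gathered by investigators unaware of allocation. Intraoperative items come from the electronic record and include hemodynamic data and, as a separate item, "use of a chronotropic agent for the treatment of bradycardia".

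**The concern.** Under the Secondary outcomes wording, two things must happen for an event: the heart rate must fall, and someone must give a drug for it. The second is a decision by a clinician who knows the arm and has no stated threshold to work to. If that decision differs between arms, the outcome differs even when the drugs do not. A real drug difference can be hidden in the same way.

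The Adverse events section, read literally, describes a different outcome under the same name, so the final report could use either.

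This matters because the Background presents fewer instances of bradycardia than with propofol as one of remimazolam's advantages. A safety comparison meant to bear on that point should not depend on treatment choices made with knowledge of the arm.

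**Working it through.** **1. The plan's own figures.** The article gives no expected bradycardia rate, so there is no plan figure to reproduce on this point. I borrow only the 330 per group from Sample size. It reproduces at an incidence of 30%: (1.96 + 0.8416)² × 2 × 0.30 × 0.70 / 0.10² = 329.7, so 330, and 330/0.95 = 347.4, so 348. At the quoted 31.1% the same formula gives 337. Nothing below alters this calculation. Intraoperative adverse events are to be analyzed per protocol, so the actual number may be somewhat smaller than 330.

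**2. What the outcome measures.** For each arm:

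observed rate = true bradycardia rate × proportion of episodes treated.

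The second factor is set in the operating room. Blinded extraction copies the product correctly but cannot separate the factors.

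**3. Illustration of the distortion (all rates assumed).** True rate 20% in both arms, with 70% of propofol and 50% of remimazolam episodes treated: 0.20 × 0.70 = 14% and 0.20 × 0.50 = 10%. The apparent relative reduction is 1 − 10/14 = 29%, with no true difference.

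**4. Chance of a nominally significant result (all rates assumed).** Equal true rates, 330 per arm, two-sided 0.05. The chance is Φ[(d − 1.96 × SE0)/SE1], where d is the difference in observed rates, SE0 the pooled and SE1 the unpooled standard error. This counts only results in the direction created by unequal treatment, for which the nominal rate is 2.5%.

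For 18% v 14%: SE0 = √(2 × 0.16 × 0.84/330) = 0.02854; SE1 = √((0.18 × 0.82 + 0.14 × 0.86)/330) = 0.02850; (0.04 − 0.05594)/0.02850 = −0.56; Φ = 0.29.

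| True rate, both arms | 90% v 80% treated | 90% v 70% treated | 90% v 50% treated |
|---|---|---|---|
| 10% | 9% v 8%: 0.07 | 9% v 7%: 0.16 | 9% v 5%: 0.52 |
| 20% | 18% v 16%: 0.10 | 18% v 14%: 0.29 | 18% v 10%: 0.84 |
| 30% | 27% v 24%: 0.14 | 27% v 21%: 0.44 | 27% v 15%: 0.97 |

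A small difference in treatment does little; a large one dominates the result. The article does not show which applies, or whether any difference will exist.

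**5. Movement grade.** Mild and severe are defined by the movement and its consequences. Moderate requires an effect on the surgery and an anesthetic response. Only that second element depends on an unblinded clinician.

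**6. Delayed extubation.** This is a time cut-off. Patients who cannot obey and patients kept intubated at the surgeon's request both count. Suppose the drug-related rate is 4% v 8% and requests add 15 points to each arm (assumed): the outcome reads 19% v 23%. The difference stays at 4 points, but the ratio falls from 2.0 to 23/19 = 1.21. At 330 per arm the unpooled standard error rises from √((0.04 × 0.96 + 0.08 × 0.92)/330) = 0.0184 to √((0.19 × 0.81 + 0.23 × 0.77)/330) = 0.0317, so difference/SE falls from 2.17 to 1.26. This is dilution, not bias by arm.

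**The case against.** The strongest defense is that treated bradycardia is a reasonable choice of clinically relevant event. The Adverse events list may simply be a short form of the fuller one, and Intraoperative data collection again pairs bradycardia with chronotropic use. The instructions in Anesthetic care are the same for both arms, and the one on bradycardia is directive. Any difference between arms in willingness to treat is conjecture, and heart-rate data are collected anyway.

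Much of this stands. Treated bradycardia is worth reporting, the discrepancy between sections may be only shorthand, and no differential treatment is demonstrated. But an identical instruction to unblinded staff, without a numeric trigger, does not ensure identical application. Collecting heart rate also does not help while the outcome ignores it.

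Four stronger readings are tempting, and the documents do not support them:

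- *That the blinding statement about anesthesiologists is false.* Giving treatment is not assessing results. Safety monitoring has them watch for adverse effects during the operation, which is ordinary care, and no section says they grade or adjudicate outcomes.
- *That delayed extubation is defined by a clinician's decision.* It is defined by time, and the surgeon who may request continued intubation is described as blinded.
- *That movement grading as a whole depends on the anesthesiologist.* Only part of one of three grades does.
- *That anticholinergics are discouraged because of delirium.* Anesthetic care gives no reason.

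**Conclusion.** The point holds for bradycardia. As defined under Secondary outcomes, the event requires a treatment decision by unblinded staff with no stated trigger, and the Adverse events section omits that requirement. The comparison can therefore be distorted in either direction, and blinded extraction does not prevent it.

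The size cannot be derived from the article. Under the assumptions above, the chance of a spurious nominally significant difference runs from 7% (true rate 10%, 90% v 80% treated) to 97% (true rate 30%, 90% v 50% treated). These figures show sensitivity and are not predictions.

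The movement and extubation points are lesser matters of clarity and dilution. The primary delirium outcome, its margin and the sample size are untouched. The change is worth making because it is cheap and protects a comparison that the Background treats as an advantage of remimazolam.

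**What to change.** 1. Reconcile the bradycardia wording in Secondary outcomes and Adverse events so that there is one named outcome.
2. Define that outcome from the recorded heart rate, already among the hemodynamic data collected, with a threshold and minimum duration fixed before unblinding. This follows the approach the protocol already takes to hypotension. The limit of 20% from baseline in Anesthetic care is a management target and need not be the outcome threshold. I propose no value, and no change to when bradycardia is treated.
3. Report bradycardia treated with a chronotropic agent separately, by arm, so that any difference in treatment is visible.
4. Grade movement by its effect on the surgery, and record the anesthetic response as a separate item.
5. Keep all patients in the delayed-extubation outcome, but record the reason (could not obey, or surgeon's request) and show the two separately.

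The cost is some outcome wording, a short analysis of existing records and one or two CRF fields. One limit remains: early treatment can also keep a recorded heart rate above a threshold, so the new definition reduces dependence on the clinician without removing it entirely. Item 3 helps to judge how much is left.
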